### Study methodology

#### Demographic and clinical characteristics

A datasheet will be completed for each participant after recruitment at T0 and at the T3 and T6 follow-up visits. Data gathered will include date of birth, anthropometric parameters (body weight, standing height, waist circumference), blood pressure, routine laboratory data (serum prostate-specific antigen (PSA), haemoglobin, white cell and platelet counts), site of metastasis, and cancer-related data (stage and Gleason grade of cancer, details of current and previous systemic and radiation therapy). Data will also be recorded from three measures of physical function including balance, lower limb strength, and gait speed. These three measures will be completed with the patient by the chartered physiotherapist. Participants may also be asked to complete a structured interview session with the chartered physiotherapist exploring attitudes towards exercise. An overview of all data collected is included in Fig. 3.

**Fig. 3 Fig3:**
[figure not shown]
ExPeCT SPIRIT figure. ^a^Natural killer cell testing will only be performed at Irish sites. *BMI* body mass index, *Circ.* Circumference, *FACT-P* Functional Assessment of Cancer Therapy scales for Men with Prostate Cancer, *NCB* needle core biopsy, *PHQ* Patient Health Questionnaire

### Primary study endpoint

#### Platelet cloaking of circulating tumour cells

For each clinical review episode (at baseline and after 3 and 6 months), 12–16 mL of blood drawn from each patient into K_2_-EDTA tubes will be filtered by a ScreenCell® Cyto kit within 4 h. CTC enrichment depends on vacuum-assisted filtration through a microporous membrane filter to separate CTCs from other blood cells on the basis of size. Three to five filters will be generated for each participant, two of which will be stained with May-Grunwald Giemsa, followed by a broad-spectrum epithelial marker, and one to three reserved for platelet cloaking assays and other relevant markers. CTCs will be enumerated cytologically. The degree of platelet adhesion to CTCs will be assessed by immunohistochemistry. The number of CTCs with adherent platelets will be counted, and the approximate number of platelets adherent to each cell will be estimated.

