### Interactions between platelets and circulating tumour cells

Despite the long-recognised association between cancer and thromboembolism, it has been unclear whether the thrombocytosis often seen in patients with metastases is a consequence or cause of widespread dissemination of the tumour. Accumulating evidence now shows that platelets support tumour metastasis by various mechanisms [20]. Platelets are involved in the arrest of CTCs in the vasculature and, through endothelial interactions, enable their extravasation. Platelets also secrete various pro-oncogenic factors including platelet-derived growth factor (PDGF) and vascular endothelial growth factor (VEGF), and mediate pro-survival signals in ovarian cancer cells [21].

Tumour cell-induced platelet aggregation correlates with metastatic potential, and may be due to “cloaking” of tumour cells by adherent platelets. The interaction between platelet cloaking of CTCs and tumour cell killing by NK cells is not completely understood. “Cloaking” of CTCs by adherent platelets may impede NK cell clearance of CTCs from the circulation, enhancing metastatic spread. Thrombocytopaenic mice exhibited reduced tumour metastatic burden when the tumour cells were NK cell sensitive, and in-vitro studies demonstrated reduced NK tumourilytic activity when platelets aggregated around tumour cells [22]. Platelets may enable evasion of immune editing by NK cells by conferring a “pseudonormal” phenotype on CTCs by encouraging high-level surface expression of normal major histocompatibility complex (MHC) class 1 antigen by the tumour cells [23].

In these pre-clinical studies there is an association between increased platelet-tumour cell interactions and endpoints of metastasis and death in animal models, but no clinical data exist as yet relating these interactions to outcomes in human disease. The current proposed study takes the current weight of evidence that platelet interactions are important in metastasis, and attempts to make the leap to demonstrate this in a clinical population. Platelet “cloaking” may be enhanced in obese patients due to the pro-inflammatory, pro-thrombotic state, and may be a mechanism for worse cancer-specific outcomes in this group.

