**Fig. 1 Fig1:**
[figure not shown]
Schematic of the four projects involved in the ExPeCT trial. *BMI* body mass index, *CTC* circulating tumour cell, *H&E* haematoxylin and eosin, *NK* natural killer, *TNF* tumour necrosis factor

Project 1: CTCs will be enumerated in the T0 samples. Adherent platelets will be quantified and compared between the exposed and non-exposed groups, and correlated with clinicopathological parameters.Project 2: The exercise group will undertake a regular supervised aerobic exercise programme, whereas the control group will not. T3 and T6 blood samples will be assessed for CTC numbers and platelet cloaking. Changes will be compared with the T0 sample, and between exposed and non-exposed, and exercise and control groups. Participants will complete a detailed questionnaire to assess QoL and other parameters at each visit.Project 3: Blood samples will be assessed for NK cell number and activation, markers of systemic inflammation, adipokines, and serum factors related to platelet activation. The prostate needle core biopsies (NCBs) will be examined microscopically for atrophy and inflammation by morphology and immunohistochemistry, with particular reference to NK cells. All variables will be correlated with platelet cloaking.Project 4: NCBs will be assessed for expression of an obesity-associated lethality gene signature (whose genes are known to play a role in obesity or platelet aggregation and coagulation), and correlated with platelet cloaking of CTCs.

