### Sample size

We will recruit 200 participants over the lifetime of the study, evenly divided between the exercise group and the control group. To calculate the power of the study, we used data from a previous study of ovarian cancer cell lines which showed approximately 2% platelet adhesion [21]. A standard deviation (SD) varying from 2% to 10% would enable us to detect a difference of platelet cloaking of between 0.79% and 3.9%. Research into this area is at an early stage and the clinical importance of specific incremental changes in the degree of platelet cloaking is as yet uncertain, but its elucidation is beyond the scope of this study.

With regard to the detection of changes in platelet cloaking with time, and taking the same assumptions regarding SD of platelet adhesion in PrCa CTCs as in project 1, we will be able to detect a change of 1.8% platelet cloaking between any two time points in the 100 participants in each of the exercise and the control groups, determined by paired *t* testing. A SD varying from 2% to 10% would enable us to detect a difference of platelet cloaking of between 0.56% and 2.8%. Generalised linear mixed models will be employed in order to account for the correlation between multiple measurements in the same experimental subject.

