### Statistical analysis

Project 1 will compare the number of cloaked platelets, comparing healthy weight and overweight men using either the *t* test or the non-parametric Mann-Whitney test, depending on the normality of the data. Linear regression models will be used to test the association between obesity and extent of platelet cloaking, adjusting for potential confounders such as age, use of medications, and smoking. If the data are not normally distributed then a log transformation will be employed. In addition to comparing overweight and healthy weight men as a binary exposure, BMI will be modelled as an ordinal variable (<18.5, 18.5–24.9, 25.0–27.4, 27.5–29.9, 30+) and as a continuous variable and to test for linear trends with the log likelihood ratio test of nested models.

Project 2 will compare measurements of platelet cloaking at baseline and months 3 and 6 follow-up time points among men randomised to the exercise and control arms, in both the exposed (BMI ≥ 25) and non-exposed (BMI < 25) groups. Intention-to-treat analyses will use linear mixed-effect models to incorporate each biomarker for a given participant over time. BMI will also be stratified to look at potential effect modification. To estimate longitudinal changes in quality of life scores from baseline, the primary analysis will be carried out using a mixed-effects model for repeated measures.

Project 3 will examine the extent of the inflammatory infiltrate in diagnostic NCBs. All variables will be correlated with CTC numbers and platelet cloaking using basic descriptive statistics such as Pearson correlation coefficients for continuous variables and simple *t* tests for categorical variables. In the event of skewed distributions or sparse data, we will use non-parametric tests such as the Spearman correlation and Mann-Whitney. Moreover, a principal component analysis will be undertaken to estimate the proportion of variability in platelet cloaking and CTC number which is explained as a function of the obesity inflammatory biomarkers. The biomarkers will be modelled as principal components in the linear regression and adjusted for potential confounders such as age, smoking, and other factors.

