Project 4: Generalized linear regression models will be used to examine whether obesity is associated with expression of each of the five markers in the tumour tissue, adjusting for potential confounders such as age and smoking status, as well as clinical features. Obesity will be dichotomised as BMI greater or less than 25, and we will also model BMI as a continuous variable and examine tests for trend. The expression of each marker will be assessed with respect to the extent of platelet cloaking (high, intermediate, and low). The categorisation of platelet cloaking as high, intermediate, and low is dependent on the proportion of CTCs with adherent platelets (high > 75%, intermediate 25–75%, low < 25%). A gene score will be created by ranking individuals across expression of each gene in tertiles, assigning points for each marker as lowest tertile = 0, middle tertile = 1, upper tertile = 2, and calculating a summary score.

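### The primary endpoint is worded on several scales, and on the percentage and per-cell scales it has no value for a sample without CTCs, so the randomised comparison would be conditional on CTCs still being present

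*Protocol article*

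**What the plan says.** All places are in the protocol article; no SAP is at hand.

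- **Primary study endpoint:** "The number of CTCs with adherent platelets will be counted, and the approximate number of platelets adherent to each cell will be estimated". This gives two measures, a count of cloaked CTCs and a per-cell platelet number.
- **Sample size:** cloaking is a percentage. The reference level is about 2%, from ovarian cancer cell lines. For SDs of 2% to 10% the detectable difference is 0.79% to 3.9%, and the detectable paired change is 0.56% to 2.8% in 100 men per arm. The section adds that "Generalised linear mixed models will be employed".
- **Statistical analysis, Project 1:** "Project 1 will compare the number of cloaked platelets, comparing healthy weight and overweight men".
- **Statistical analysis, Project 2 (the randomised comparison):** "Intention-to-treat analyses will use linear mixed-effect models".
- **Statistical analysis, Project 4:** the cloaking categories are "dependent on the proportion of CTCs with adherent platelets".
- **Study design, Project 2:** "T3 and T6 blood samples will be assessed for CTC numbers and platelet cloaking".

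The inclusion and exclusion criteria do not ask for detectable CTCs. The article does not say how a sample without CTCs enters the analysis.

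**The concern.** A percentage of CTCs, or a platelet number per CTC, needs at least one CTC. At T3 and T6 the presence of CTCs is itself an outcome that exercise might change. A linear mixed model of the percentage would use only visits with CTCs. The arms would then be compared among samples selected after randomisation, which the intention-to-treat label does not convey. The same model would treat a percentage from one cell as being as informative as one from fifty.

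The background makes the selection more than a formality. It says cloaking "may impede NK cell clearance of CTCs from the circulation", and the section on natural killer cells reports that NK cells respond to exercise. If training removed uncloaked cells preferentially, the share cloaked among the survivors would go up, whereas the trial's second hypothesis expects exercise to reduce cloaking. At stake are the direction and the precision of the main randomised result.

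**Working it through.** **1. The plan's own figures.** The article states neither alpha nor power. With two-sided 5% and 80% (assumed), z-sum = 1.960 + 0.842 = 2.802.

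- Two groups of 100: 2.802 × SD × √(2/100) = 0.79 (SD 2) and 3.96 (SD 10). Stated: 0.79 and 3.9.
- Paired, n = 100: 2.802 × SD / √100 = 0.56 and 2.80. Stated: 0.56 and 2.8.

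The figures reproduce, and they use every man, with no allowance for samples without CTCs.

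**2. Fewer evaluable pairs.** The article gives no rate *p* of CTC-free samples, so *p* is assumed. If absence is independent between two visits, pairs = 100 × (1 − p)². If the same men lack CTCs at both visits, pairs = 100 × (1 − p). The detectable change at SD 2% is 2.802 × 2 / √pairs = 5.604 / √pairs.

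| p | Pairs, independent | Change | Pairs, same men | Change |
|---|---|---|---|---|
| 0 | 100 | 0.56% | 100 | 0.56% |
| 20% | 64 | 0.70% | 80 | 0.63% |
| 30% | 49 | 0.80% | 70 | 0.67% |
| 40% | 36 | 0.93% | 60 | 0.72% |

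**3. Weighting.** The sampling SD of a proportion from *n* CTCs is √(c(1 − c)/n). At c = 2%, it is √0.0196 = 14% for 1 CTC and √(0.0196/50) = 2.0% for 50 CTCs. The sampling variances differ 50-fold, yet a linear model of the percentage gives both samples the same residual variance. Differences between men would reduce the contrast in ideal weights but not remove it.

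**4. Direction.** Let *c* be the cloaked share of cells shed, and *s* the survival of uncloaked relative to cloaked cells. The observed share is c / (c + (1 − c)s). The values of *s* are assumed; only c = 2% has a counterpart in the article.

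| c | s = 0.50 | s = 0.25 (more clearance, same cloaking) | c cut by 20%, s = 0.50 (less cloaking only) |
|---|---|---|---|
| 2% | 3.9% | 7.5% | 3.1% |
| 25% | 40% | 57% | 33% |
| 50% | 67% | 80% | 57% |

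In the third column the number of cloaked CTCs is unchanged and total CTCs fall, so the share rises with no more cells cloaked. In the last column the share falls, as it should. With both effects at c = 2%, the share is 0.016 / (0.016 + 0.984 × 0.25) = 6.1%. That is still above 3.9%, although cloaked CTCs are down 20%.

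**5. Missingness by arm.** Take 5 cells shed on average and c = 2%. Mean CTCs are 5 × (0.02 + 0.98 × 0.50) = 2.55 and 5 × (0.02 + 0.98 × 0.25) = 1.325. Under a Poisson model, samples without CTCs go from e^−2.55 = 8% to e^−1.325 = 27%. With overdispersed (gamma-Poisson, shape 1) counts they go from 28% to 43%. Scoring those samples as 0% does not cure the direction problem: in the overdispersed case the mean share still rises, from 2.8% to 4.3%.

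**The case against.** Several objections stand.

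- The endpoint section names a count of cloaked CTCs first, and that count is zero, not missing, in a man without CTCs. A reader might infer that cloaking is defined only on surviving CTCs. That is true of the percentage and per-cell forms, not of every form.
- A reader might infer that men without CTCs are dropped from the primary analysis. The article does not say so, and a rule for such samples could sit in the full protocol or SAP. Exclusion follows only if the percentage or per-cell value is what the linear model analyses.
- A reader might infer that, by the trial's own mechanism, a benefit of exercise will show up as more cloaking. The documents do not support that. The NK data concern mainly acute or brief exercise, plus hypoxic training in healthy young men, and the article calls the interplay of cloaking and NK killing incompletely understood. The route the trial sets out runs through inflammation to less cloaking, and on that route the direction stays right.
- A mixed model uses all available visits, so the pair counts bear on the paired power statement more than on the final model.
- Naming linear models in one section and generalised linear ones in another carries little weight, since the first is a special case of the second. The paired t test serves only the power calculation.
- The proportion categories belong to Project 4, not to the randomised comparison.
- Cloaked CTCs per mL also fall when systemic therapy lowers total CTCs, so as the sole primary measure they would not answer the cloaking hypothesis.

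The objections do not remove the core. The power statement is on the percentage scale, the scale differs between sections, and the choice of scale decides whether the comparison is conditional on CTCs being present. A zero rule alone does not repair the denominator. CTC numbers are measured at the same visits but are not tied to the interpretation of cloaking.

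**Conclusion.** The concern holds in a limited form and is worth acting on. The article does not fix one scale for its primary endpoint. On the percentage and per-cell scales, a linear mixed model would be conditional on a post-randomisation result, would ignore how many CTCs each value rests on, and would have fewer than the 100 pairs assumed.

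The loss of precision depends on a CTC-free rate that the article does not give. At 20% to 40% per visit, the detectable change at SD 2% is 0.63% to 0.72% if the same men are affected, and 0.70% to 0.93% if absence is independent, against 0.56% stated. A change of sign is possible only if exercise increases clearance of uncloaked cells. It is a risk to guard against, not a predicted result.

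**What to change.** 1. Use one scale for cloaking in the primary endpoint, sample size and statistical analysis sections.
2. Analyse the cloaked proportion with a binomial mixed model (cloaked out of total CTCs, random effect for participant), labelled as conditional on CTCs being present. This fits the generalised linear mixed models already named in the sample size section.
3. For exercise versus control, report beside it count mixed models in all randomised men for cloaked CTCs and for total CTCs. Score zero when none are found, and use an offset for the blood volume or number of filters assayed. Do not interpret the proportion alone.
4. State in the sample size section that the detectable differences assume every sample contains CTCs.

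**Cost:** wording in the analysis plan, on counts the trial already makes. The volume or filters assayed must be on record, because the number of filters reserved for cloaking assays and other markers varies from one to three. The cloaked count mixes CTC number with cloaking, so the three results have to be read together.

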### Secondary study endpoints

#### Systemic and localized tumour inflammation and coagulability

This part of the project consists of measurement of systemic and prostate inflammation, markers of coagulation, cytokines, and NK cells. The substrates for this work will be blood samples taken from each participant at T0, T3, and T6, and the original diagnostic NCB paraffin tissue blocks. Examples of the serological and haematological tests include adiponectin, leptin, and resistin.

#### Expression of lethality-associated genes

This project will evaluate expression of selected genes known to be associated with PrCa progression, coagulation, and stem cell-like phenotype in diagnostic NCBs. Sections of formalin-fixed, paraffin-embedded tissue blocks will be cut from each patient’s diagnostic prostate NCB specimen. These sections will be dissected by either laser capture microdissection or gross dissection. Ribonucleic acid (RNA) will be extracted from the microdissected tissue. Gene expression profiling will be undertaken on diagnostic biopsy material using custom-designed assays designed to detect only mRNA and to traverse the exonic junction. Assays for the genes CXCR4, PLA2G7, PTGER1, AVPR2, and HTR2B will be employed. Quantitation of results of polymerase chain reaction (PCR) will be undertaken using the ΔΔCt method, comparing the Ct values of the samples of interest with a control or calibrator such as a non-treated sample or RNA from normal tissue. Diagnostic material may be used for further gene expression analysis associated with obesity as part of the trial.

#### Quality of life assessment

All participants will complete a detailed questionnaire after recruitment at T0, and again at T3 and T6. The sections of the questionnaire are as follows:Background details (age at diagnosis, domiciliary situation, comorbidities, recent medications).Smoking and alcohol.Sleep (Pittsburgh Sleep Quality Index [31]).Stress (Perceived Stress Scale – 4).Depression (Patient Health Questionnaire (PHQ)-9) [32].Quality of life (FACT-P) [33].Memory and cognition.Physical activity.Diet (dairy products, meat, vitamin D).Pain (Brief Pain Inventory Scale) [34].

Some sections of the questionnaire are stand-alone validated instruments (such as the Functional Assessment of Cancer Therapy scales for Men with Prostate Cancer (FACT-P), which is designed to assess health-related quality of life in this setting [33]). Others, such as the sections on physical activity and diet, are derived from a prostate cancer-specific questionnaire used in the large Physicians’ Health Study based at Harvard University [35].

### Exercise programme

The exercise group will participate in a 6-month moderate-to-vigorous intensity aerobic exercise programme comprising a weekly class and a home-based aerobic exercise programme. Participants will also be encouraged to complete weekly activity diaries. From T0 to T3, participants in the exercise arm will meet in small groups with a chartered physiotherapist for 1 h per week. During the first class the participants will receive an introduction to the format of the exercise and will be educated on safe exercise practices and strategies to monitor exercise exertion.

Each exercise participant will receive, and be educated about using, a Polar heart rate monitor for the duration of the study. Participants will exercise to a prescribed heart rate range during class and home sessions. Exercise prescription will progress in intensity and duration during months 1 and 2 of the programme to reach the target 3 h per week (180 min/week) of moderate-to-vigorous intensity activity from month 3 onwards (Table 1). This level of activity has been previously shown to be associated with a 33% reduction in all-cause mortality following prostate cancer [36]. Participants will be encouraged to achieve this target exercise in six 30-min sessions throughout the week. However, flexibility will be allowed to facilitate longer or shorter session to a total of 180 min/week. Each exercise session must be of at least 10 min duration. The research team has previously shown that similar aerobic activity intensities can be achieved in cancer survivors through a home-based walking programme and that a Polar heart rate monitor was an acceptable means of monitoring activity intensity [37].

**Table 1 Tab1:** Exercise intensity during supervised classes

Supervised exercise classes		Exercise intensity (% heart rate reserve) by baseline fitness group			Duration
		Poor	Fair	Average	(min)
Month 1	Week 1	40–50%	50–60%	55–65%	20
	Week 2	40–50%	50–60%	55–65%	20
	Week 3	45–55%	55–65%	60–70%	20
	Week 4	45–55%	55–65%	60–70%	30
Month 2	Week 5	50–60%	60–70%	65–75%	30
	Week 6	50–60%	60–70%	65–75%	30
	Week 7	55–65%	65–75%	65–75%	30
	Week 8	55–65%	65–75%	65–75%	30
Month 3	Week 9	60–70%	65–75%	65–75%	30
	Week 10	60–70%	65–75%	65–75%	30
	Week 11	60–75%	65–75%	65–75%	30
	Week 12	60–75%	65–75%	65–75%	30

During months 1–3, data from the Polar heart rate monitor will be downloaded weekly to monitor adherence. Participants will be scheduled to attend the research centre once monthly from T3 to T6 to download data and encourage ongoing adherence to the programme. In addition, participants will receive weekly telephone contact from the ExPeCT research team from T3 to T6 to encourage adherence.

The control group will not be given specific advice regarding exercise beyond that considered usual medical care, and will not be invited to participate in the aerobic exercise group. Participants will be reviewed at T3 and T6 following the baseline visit and anthropometric measurements and further blood samples taken. Participants assigned to the control group will be offered a personal exercise advice session following completion of the T6 assessment.

